### Patient and public involvement

Patients were involved in the design of the educational programme. When designing the intervention we anchored the patient participation in the project approach by relying on the results of focus groups among 50 patients from the intended target group. Their opinion was sought regarding two methods described in the literature of additional information/coaching: (1) an additional telephone consultation by the transplant doctor^10^ and (2) home education where family and friends are invited to receive knowledge about RRT. Eighty-eight per cent of the participants favoured the home-based education over the telephone consultations.^11^ Additionally, a patient panel and organisations were involved in the development of the educational programme protocol and materials. Patients were not involved in the design of the cost-effectiveness study.

### The intervention: home-based education

The intervention consists of two sessions at the patient’s home. The intervention is carried out by allied health transplantation professionals and psychologists. In the first session, the goals of the educational programme are discussed and the home-based educational meeting will be prepared. The educators will make an inventory of individuals in the patient’s social network using a sociogram. This helps open the discussion on who to invite for the second session, the home-based educational meeting. The need for an independent translator is also discussed.

In the second session, the education takes place. The educators organise this session in such a way that they will do ‘whatever it takes’, in line with one of the basic principles of MST, to make this event as patient tailored as possible.^6^ The primary goal of this intervention is educational, therefore, it is not necessary that all the invitees are or become potential donors. The intervention is based on the previous RCT and cross-over studies.^3 4^ A more detailed description can be found in a published protocol manuscript.^12^

### Measures

*Knowledge and communication* are evaluated through questionnaires among all patients and for at least one relative/friend in attendance at the home-based educational session. The knowledge about renal disease and RRTs is measured through a validated knowledge questionnaire R3K-T. This 21-item knowledge questionnaire has been developed specifically for kidney disease, and has good psychometric properties.^13^ Answer categories are multiple choice and the number of correct answers is summed. The three-item communication questionnaire can be answered on a scale from 1 (completely disagree) to 5 (completely agree). An example item is ‘I can talk about renal replacement therapies with my loved ones.’ Finally, we assess patients’ and invitees’ attitude towards RRT through a nine-item questionnaire. This questionnaire can also be answered on a scale from 1 (completely disagree) to 5 (completely agree). An item example is ‘I am afraid donation will harm the health of the donor.’ The administration of questionnaires will take place at two occasions: (1) prior to the education either during an outpatient visit after signing the ‘informed consent form’ or during the first session; and (2) shortly after the second session.

*Protocol adherence measures*: After every completed home intervention an independent telephone evaluation is conducted with the patient and a relative/friend who attended the education programme, to measure the degree of protocol adherence of the educators. The independence is guaranteed through an independent party, specialised in treatment adherence measurement (www.Praktikon.nl). Protocol adherence in this implementation is defined as the extent to which the different teams carry out the educational programme as described in the protocol. Measurement is done with an adaptation of the ‘Treatment Adherence Measures’ (TAM) questionnaire.^14^ TAM is scored on a 0–1 scale, where 1 stands for complete protocol adherence. The results of the TAM can be used for research purposes and to give the educators feedback on the quality of their interventions during the implementation phase.

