**Methods and design:**

Patients with ESRD who do not have a living kidney donor are eligible to receive the home-based educational intervention. This is carried out by allied health transplantation professionals and psychologists across eight hospitals in the Netherlands. The cost-effectiveness analysis will be conducted with a Markov model. Cost data will be obtained from the literature. We will obtain the quality of life data from the patients who participate in the educational programme. Questionnaires on knowledge and communication will be used to measure the outcomes of the programme. Data on LDKT activities will be obtained from medical records up to 24 months after the education. A protocol adherence measure will be assessed by a third party by means of a telephone interview with the patients and the invitees.

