If patients have not been able to find living donor candidates in their social network, they will be asked whether they and their social network wish to receive home-based education from healthcare educators. The nephrologist explains to the patients that the educators will provide information about renal diseases, the different types of RRT and their impact on quality of life. Furthermore, the educators can help to discuss the possibilities of living donation within the social network of the patient. If the patient consents to the intervention in consultation with his/her nephrologist, the healthcare educators contact the patient to make an appointment for the first home session. Patients are supported in inviting their family/friends to the second educational session. After completion of the programme, an evaluation consultation is planned with the nephrologist. The number of patients who do not consent to participate in the study is recorded, as well as the reason for non-participation.

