### Quality assurance

This study has also implemented a central quality assurance system. We hypothesise that the effectiveness is moderated by the protocol adherence of the team of healthcare professionals. In the implementation study, it might be possible that there are differences in the way teams and centres adhere to the protocol. Protocol adherence measures will be assessed by a third party by means of a telephone interview with the patients and the invitees. Patients and invitees are asked for their opinion and level of satisfaction regarding the way in which the intervention was delivered. Patients and invitees are asked to answer the 15-item TAM scoring list. Items are rated on a Likert scale (1 not at all to 5 very much). Only items that are rated with a 5 will be regarded as fully adherent. Items scored with a 1–4 will be regarded as non-adherent. The outcome of the protocol adherence will be associated with the gain in knowledge and communication skills. We will also look if there is a correlation between the protocol adherence and the amount of LDKTs. A part of the quality assurance is a training that all professionals who conduct the home interventions must take part in. During this training, issues are discussed such as: how to convey uniform and complete information to the patient, how to behave during the home visits, how to create an alignment of the goals of the home visit with the patients, how to assist the patient in inviting friends and relatives, how to deal with emotional moments, how to discuss delicate topics with respect to individual feelings and opinions and, finally, how to ensure no detrimental psychosocial effects of the education occur for the patients and his/her family/friends. All these aspects can be executed in different ways by the educators. A supervisor evaluates the home visits with each team separately every 6 weeks and discuss difficult cases. After these meetings the supervisor is graded by the educators through a 10-item questionnaire regarding the content of the teaching and the interpersonal delivery of the supervisor. Furthermore, the supervisor will bring together all educators for a so-called intervision meeting every 3 months. These intervision sessions are meant to discuss the home visits with each other in order to learn from each other and to keep the procedures similar.

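### The adherence–outcome analysis rests on measures that exist only for patients who complete session 2, although reaching session 2 is partly a result of how well the programme is delivered

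*Protocol article*

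**What the plan says.** The intervention section of the protocol article describes two steps: "The intervention consists of two sessions at the patient’s home". Session 1 sets goals, maps the social network and prepares the meeting. Then: "In the second session, the education takes place".

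The measures for the second objective are timed as follows.

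- **Adherence** (the Treatment Adherence Measures score, TAM), under Measures: "After every completed home intervention an independent telephone evaluation is conducted with the patient and a relative/friend who attended the education programme". Quality assurance names the same respondents: "Protocol adherence measures will be assessed by a third party by means of a telephone interview with the patients and the invitees".
- **Knowledge and communication**, under Measures: the first questionnaire comes before the education or during session 1. The other occasion is "2) shortly after the second session".
- **LDKT activities**, in the Methods and design part of the Abstract: "Data on LDKT activities will be obtained from medical records up to 24 months after the education".

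The step that links the two sessions is treated as part of delivery. Participants and procedure says: "Patients are supported in inviting their family/friends to the second educational session". The training listed under Quality assurance includes "how to assist the patient in inviting friends and relatives", and the article adds that educators may carry out such aspects in different ways.

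Quality assurance then plans to relate adherence to the gain in knowledge and communication, and to look for a correlation with the number of LDKTs.

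**The concern.** A patient can enter the programme, have session 1 and never reach session 2. One possible reason is that the invitation step was poorly supported, and this is part of the delivery quality that the second objective sets out to study. Such a patient would contribute nothing to the planned associations. The analysis would then compare adherence and outcome only among patients for whom delivery worked well enough to bring about session 2.

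The result is meant to carry weight. Under Hypotheses, a demonstrated link between adherence and effect is the ground for making quality assurance inseparable from the programme, and the Discussion connects adherence with reimbursement. A team that loses many patients after session 1 could look as adherent and as effective as a team that loses none, and the planned measures would not show the difference.

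**Working it through.** The article gives no completion rate, expected adherence effect, sample size or power for this analysis, so there is no stated figure to reproduce. The check has three parts.

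**1. What is available for a patient who has session 1 but not session 2**

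| Measure | Timed to | Available? |
|---|---|---|
| TAM | completed intervention, with an attending relative or friend | no |
| Knowledge and communication, first value | before the education or at session 1 | yes |
| Knowledge and communication, second value | after session 2 | no, so no gain score |
| LDKT | 24 months from the education | in the records, but the window has no clear start |

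Averaging TAM by team would not remove the problem, because the average would still come from completers.

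**2. Illustration with assumed rates**

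From Participants and procedure: four university centres with about 50 patients a year and four regional hospitals with 20, over 2 years. If both figures are yearly, 2 × (4×50 + 4×20) = 560 patients; if the 20 is not yearly, 2×4×50 + 4×20 = 480. The risk ratios below do not depend on this total.

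Assumptions, none from the article: half of 560 patients are with better-delivering teams and half with poorer-delivering teams; LDKT is 5% in non-completers. With completion c and LDKT among completers p:

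LDKT per patient started = c × p + (1 − c) × 0.05

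Number lost = 280 × (2 − c for better teams − c for poorer teams)

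With p = 20% in both groups, so that completers show a risk ratio of 1.00:

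| Completion, better / poorer | Lost of 560 | LDKT per patient started | Risk ratio |
|---|---|---|---|
| 95% / 95% | 28 | 19.3% / 19.3% | 1.00 |
| 95% / 85% | 56 | 19.3% / 17.8% | 1.08 |
| 95% / 75% | 84 | 19.3% / 16.3% | 1.18 |
| 90% / 60% | 140 | 18.5% / 14.0% | 1.32 |

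The last row in full: 0.90×0.20 + 0.10×0.05 = 0.185; 0.60×0.20 + 0.40×0.05 = 0.140; 0.185/0.140 = 1.32.

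With p = 25% against 20% (risk ratio 1.25 among completers), the same four completion patterns give 1.25, 1.35, 1.48 and 1.64 per patient started.

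**3. Direction**

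A simulation of 2 million patients let patient motivation raise both completion and LDKT, and varied how strongly delivery quality affected completion. Between 75% and 78% completed. The correlation of quality with LDKT was:

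| Effect of quality on completion | All started | Completers | Ratio |
|---|---|---|---|
| none | 0.099 | 0.112 | 1.13 |
| moderate | 0.122 | 0.099 | 0.82 |
| strong | 0.140 | 0.086 | 0.61 |

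The completer-only correlation is weaker when quality drives completion and somewhat stronger when it does not.

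**The case against.** Several counter-arguments have force.

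- **The loss and its cause are inferred.** The article does not say that patients stop between sessions, how many do, or why. Illness, a deceased donor offer or a donor who comes forward early are other possible reasons. Poor invitation support may also show among completers, as few invitees or low TAM ratings. This stands, and it is why no size can be claimed.
- **The LDKT window can be read more widely.** The Abstract sentence is short, and the article sometimes uses the word education for the whole programme. Since LDKT comes from medical records, non-completers could be counted. This is right as far as feasibility goes, but the text does not say so, and TAM and the gain scores remain limited to completers.
- **Adherence among recipients is a legitimate question.** It is, provided that the result is labelled as such. It does not answer whether delivery quality affects what happens to patients who start.
- **Recording of drop-out may be in the full protocol.** The article says that non-consent is recorded; it does not say that nothing else is. The absence of a drop-out log is therefore no part of this point.
- **An adherence score from session 1 alone would not be comparable.** TAM has 15 items and is answered by patients and invitees. Merging a partial score without an invitee into it would mix two measures. This stands and limits the remedy.

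**Conclusion.** The point holds as one of conditioning. By the timing that the article fixes, the planned associations of adherence with knowledge, communication and LDKT are conditional on completing session 2, and completion is plausibly influenced by delivery. If it is, the association may be distorted. The risk ratios of 1.00 to 1.32 per patient started, where completers show 1.00, only illustrate what assumed completion gaps of 0 to 30 percentage points would do.

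Two stronger readings are tempting and are not supported. A reader might infer that the association is biased towards no effect. That follows only if delivery quality drives completion, which the article does not show; in the simulation the ratio ran from 0.61 to 1.13 depending on that premise. A reader might also infer that the cost-effectiveness result overstates the yield per patient started. The Markov model takes its effect size from earlier studies (Table 1 and Outcomes), and intervention costs are recorded per centre, so no LDKT rate per completer enters it. The consequence is confined to the second objective.

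**What to change.** 1. Start the 24-month LDKT window at session 1 for every consenting patient who has session 1. For completers this window ends no later than one that starts at session 2, so no longer follow-up is needed. For the others it means reviewing medical records, a source the study already uses.
2. Analyse completion of session 2 per team as an implementation outcome. This needs only the dates of the two sessions.
3. Relate team-level adherence and team-level completion to LDKT per patient started. With eight hospitals, this comparison will be imprecise and should be reported as such.
4. Present the patient-level associations of TAM with knowledge, communication and LDKT as conditional on completing session 2.
5. Optionally, have the independent party hold a short interview with patients who stop after session 1, about that session and the invitation support. Report it separately and do not merge it into the 15-item TAM score.

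Items 1 to 4 cost little. Item 5 costs one short extra call per non-completer.

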### Cost-effectiveness

#### Costs

The latest published research on costs of dialysis and transplantation in the Netherlands dates back from the late 1990s.^7^ Currently, research on costs of dialysis and transplantation is in its final phase. We will use this forthcoming data ([name], personal communication). This cost data is of high quality, as it is based on the national database of insurance companies from 2014, which consists of records from 99% of all Dutch citizens. Cost calculations will include costs of dialysis modality, dialysis access, transplant procedure, other hospital costs, primary care costs, mental healthcare, medication outside the hospital, medical devices, healthcare abroad, transport and other costs. Healthcare costs for transplantation include preparatory research, transplant operation, guidance, after care, donor expenses, dialysis procedure, other hospital costs, primary care, mental healthcare, medication outside hospital, medical devices, healthcare abroad, transportation and other costs. These include all the healthcare costs associated with RRT. Since it is recommended that cost-effectiveness analysis is conducted from a societal perspective, we also aim to calculate the productivity costs.^15^ Productivity costs will be estimated with the friction cost method, as recommended in the Dutch guidelines for economic evaluation.^16^ Besides that the work situation of patients participating in the study is recorded, some research has been done regarding labour participation of patients with ESRD.^17 18^ The costs of the home-based intervention and the quality assurance will be estimated on the basis of the current practice in the implementation. Informal care costs will be estimated from the literature.^19^ The costs of the intervention are recorded per centre.

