#### Markov model

To assess the cost-effectiveness of the implementation of the home-based educational programme, we will build a ‘Markov simulation model’. This model will assess the costs and effects of ESRD treatments as it simulates the course of treatment and disease of the patients. The model will have a similar structure as a previously published model on this population,^7^ with some important updates and improvements. Unlike that Markov model, which used multivariate and univariate sensitivity analyses,^7^ our model will include probabilistic sensitivity analysis using Monte Carlo simulation. Consequently, uncertainty of all values is considered simultaneously, and the uncertainty in each parameter is assumed to possess a probability distribution.^22^ The model will run 10 000 simulations in Microsoft Excel, V.2010. By using probabilistic sensitivity analyses we follow current guidelines in health economics.^16 23 24^ A Markov modelling technique is applicable because the decision problem involves risk that is continuous over time, the timing of events is important and events may happen more than once.^25^ Within a Markov simulation, the time horizon of the study is divided into a number of discrete time periods, the so-called Markov cycles. A Markov process is based on the idea that patients are always in a certain disease state and that they can change between disease states once during each cycle. By assigning effects to each disease state and keeping track of the time patients remained in each disease state, long-term effects can be calculated. For this cost-effectiveness analysis the effects and cost per health state do not change because of the intervention. We expect that there will be more LDKTs because of the intervention. Therefore, besides the costs of the programme, only the transition probabilities will change because of the intervention and will be the only difference between the baseline and the post implementation situation. Table 1 shows an overview of the parameters used and the source.

**Table 1 T1:** Overview of parameters and sources in the Markov model

Parameter	Sources
Costs Medical costs Intervention costs Costs of productivity losses Informal care costs	Cost study of RRT in the Netherlands by [name] *et al* (forthcoming) Are recorded in the current implementation study Work situation of patients is recorded in the implementation study and use of (Dutch) literature.^16 17^ Will be estimated from existing literature^18^

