### Ethical considerations

Another challenge that we face is the ethical consideration of promoting living kidney donation through a home-based intervention. Previous studies on the ethics of this argued that such promotion is justified only when the conditions are met, such as (1) participation must be completely voluntary throughout the intervention, (2) no undue pressure should be put on the participants, (3) the education is neutral and non-directive, and (4) the purpose and the procedure should be clear to all participants.^28 29^ That does not mean there are no negative consequences whatsoever, but it does mean that the positive outcomes outweigh the negative. It could well be that a patient and/or a donor may regret the decision to have undertaken a transplantation with a kidney of a living donor, and that the donor and/or patient, in hindsight, may have felt undue pressure to donate a kidney. Adherence to the protocol will minimise these potential negative effects. However, it is possible that regret or pressure could lead to negative publicity for the programme. That is a risk since such negative publicity could impede the chances of implementing the programme as standard care.^30^ Especially considering that deceased organ donation is currently subject to controversy in the Netherlands since the government and parliament have accepted a donor law. This law is an opt-out system entailing a positive ‘no-objection’ deceased donor organ donor registration as a default for all Dutch citizens.^31^ Given this potential harm due to negative publicity it is crucial to have (1) a protocol which is justifiable from a medical ethical perspective, (2) widespread support from the various organisations involved, and (3) a high quality in terms of protocol adherence and trained adequate educators. If these conditions are met, the quality of the process then justifies its outcome, which is a subtle trade-off between positive and negative outcomes.

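### Living donors enter the economic model only as a healthcare cost; their health loss and lost work are not among the named inputs, which tilts the result towards the programme

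*Protocol article*

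**What the plan says.** The Markov model section of the protocol article states that costs and effects per health state do not change with the intervention. Apart from programme cost, the two strategies differ only in transition probabilities, and the expected change is more LDKTs.

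- **Costs, healthcare.** The Costs section lists: "Healthcare costs for transplantation include preparatory research, transplant operation, guidance, after care, donor expenses". This is the only place where a donor enters the economic inputs. The medical cost data come from insurers: "it is based on the national database of insurance companies from 2014".
- **Costs, productivity.** The reason for including them is given as: "Since it is recommended that cost-effectiveness analysis is conducted from a societal perspective, we also aim to calculate the productivity costs". The friction cost method will be used. The sources are introduced with: "Besides that the work situation of patients participating in the study is recorded, some research has been done regarding labour participation of patients with ESRD". The matching entry in Table 1 reads: "Work situation of patients is recorded in the implementation study and use of (Dutch) literature".
- **Effects.** The Abstract says: "We will obtain the quality of life data from the patients who participate in the educational programme". The Effects section and Table 1 agree: the EQ-5D-5L is given to patients at baseline and at 6, 12 and 24 months, and Table 1 lists no other source of QALYs.
- **States.** The Markov states section defines them by the patient's treatment modality, split into first and later years. No donor state or donor event is described.
- **Discussion.** Ethical considerations accepts that "the donor and/or patient, in hindsight, may have felt undue pressure to donate a kidney". The Limitations section does not mention donor outcomes.

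**The concern.** Every QALY that the model credits to the programme depends on an added LDKT, and every added LDKT means that another person has a kidney removed. The plan counts that person's healthcare cost. It names no input for that person's health loss or time off work. The boundary is uneven: productivity is brought in for a societal reason, but the named sources stop at the patient.

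If donors lose any health or working time, the omission raises incremental QALYs and lowers incremental societal cost. Both errors favour the programme, and both grow in proportion to its effect on LDKT. The planned sensitivity analyses would not show this. The probabilistic analysis varies the parameters that are in the model, and the analysis described under Outcomes varies the effect size. Neither can reveal a term that is absent. The results are meant for the Dutch National Health Care Institute and are to support adoption as standard care, so a reader should be able to see what was and was not counted.

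**Working it through.** **Inputs from the protocol article**
- Introduction: 17 versus 4 LDKTs, p=0.003, in the randomised trial of 163 dialysis patients. Arm sizes are not given.
- Abstract: four times more LDKTs.
- Outcomes section: the model takes its effect size from that trial.

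**Is a near-equal split consistent with the stated figures?**
- 82 educated and 81 controls: ratio (17/82)/(4/81) = 4.2; Fisher p = 0.0041; uncorrected chi-square p = 0.0026.
- 81 educated and 82 controls: ratio 4.3; Fisher p = 0.0022; uncorrected chi-square p = 0.0021.

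Both splits agree with p=0.003 and with a fourfold effect, so near-equal arms are a reasonable assumption.

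**Extra living donors per educated patient, r**
- Equal split: r = (17 − 4)/81.5 = 0.16.
- 82/81: 17/82 − 4/81 = 0.207 − 0.049 = 0.158.
- 81/82: 0.161.
- Wider splits, 86/77 to 77/86: 0.146 to 0.174.

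**How a donor loss enters the result.** Let q be the QALY loss per donor and c the productivity cost per donor. As planned, the ICER is ΔC/ΔE. With donors counted it is

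(ΔC + r·c) / (ΔE − r·q).

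At a willingness to pay λ, the incremental net benefit per educated patient falls by r·(λ·q + c). For any q or c above zero, this moves against the programme.

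**Illustration.** The documents give neither q nor c. All per-donor values below are assumptions, and the results are per educated patient with r = 0.16.

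| Assumed loss per donor | Omitted per educated patient |
|---|---|
| 0.02 QALY | 0.003 QALY |
| 0.10 QALY | 0.016 QALY |
| 0.25 QALY | 0.040 QALY |
| EUR 1,000 lost productivity | EUR 160 |
| EUR 10,000 lost productivity | EUR 1,600 |

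As a proportion, r largely cancels. If the patient-side gain per extra LDKT is g, then ΔE is roughly r·g, and QALYs are overstated by a fraction of about q/g of that gain. The documents do not give g, so the relative bias cannot be calculated.

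**The case against.** The strongest reply is that patient-only effects are an openly declared scope. The model is said to follow the treatment and disease course of patients, and the article is consistent about where QALYs come from. Taking effects beyond the patient is then a modelling preference, and a one-off donor value could sit in a fuller model specification that is not shown. This stands in part. It is a reason not to impose a donor-inclusive base case. It does not remove the point, because the article positively names its effect source as patients and offers Table 1 as its overview of parameters and sources.

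Three stronger readings are tempting, and the text does not carry them.

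- **That the plan commits to a full societal perspective and contradicts itself.** The wording is softer: the perspective is recommended, and productivity costs are an aim.
- **That donor work loss is certainly excluded.** The productivity row in Table 1 is not limited to patients and adds unspecified Dutch literature. The Costs section describes such research as concerning patients with ESRD, so exclusion is the more natural reading, but it is less certain than for QALYs. Donor expenses and other costs are also undefined. They stand in a healthcare list backed by insurer data, so they may cover some care for donor complications but are unlikely to cover lost work.
- **That the authors recognised donor morbidity and then dropped it.** Ethical considerations speaks of regret and pressure as ethical and publicity risks, not of health loss or absence from work.

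It is also fair to object to scaling the figure up. Multiplying 0.16 by the target volume would apply a dialysis-trial effect to patients not yet on renal replacement therapy. The evidence for them is the cross-over study, for which the article gives no LDKT contrast with a control group. The Discussion also warns that effects may differ elsewhere and that recruitment targets may be missed. For that reason no programme total is claimed here.

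**Conclusion.** The point holds as an omission that works in one direction. Followed as written, the analysis counts the donor's healthcare cost but has no named input for donor health loss, and probably none for donor work absence. The incremental result is then too favourable by about 0.16 times the per-donor loss for each educated patient. That multiplier assumes near-equal arms (0.146 to 0.174 across the wider splits above), applies to the dialysis-trial effect only, and takes the trial difference as the number of extra donors.

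A reader might infer that counting donors would overturn the cost-effectiveness conclusion. The documents do not support that. They give no per-donor loss and no recipient gain to set beside it, and the bias may be small in comparison. This is a cheap improvement in completeness and transparency. Confidence is higher for the QALY half than for the productivity half.

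**What to change.** At entry to the first-year LDKT state, add two inputs to the model and to Table 1:

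1. a one-off donor QALY decrement;
2. donor work absence, applied to donors in paid work and valued by the friction cost method already chosen.

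Give each a literature-based distribution and carry both through the 10 000 simulations. Report the result as a prespecified societal analysis beside the patient-only result, and label the latter as excluding donor outcomes. State what donor expenses cover, so that care for donor complications is not counted twice, and say whether the Dutch literature in Table 1 includes donor absence. If the programme turns out to be cost-saving, compare the two analyses by incremental net benefit, since a negative ICER is hard to interpret.

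The cost is two more literature inputs in the spreadsheet and a possibly slightly less favourable ICER. No new data collection is needed.
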